### Step 3: follow-up monitoring

Telephone follow-up monitoring will be systematically provided for one-year to monitor suicide risk and the continuity of care by the SMHI professional in close collaboration with psychiatrists. The monitoring contacts take place at five fixed times, i.e. 6 weeks after registration in the monitoring system, and after 3, 6, 9 and 12 months. In the monitoring contacts, the suicide risk will be assessed and the person will be asked if he/she is receiving SMHI care. If the person *is* receiving SMHI care, and the suicide risk is low, their clinician will be informed by mail about the suicide risk assessment or the person will be advised to inform their clinician him/herself. In case of a high suicide risk, the clinician will be immediately informed by phone. If the person is *not* receiving SMHI care, and the suicide risk is low, their general practitioner will be informed about the suicide risk assessment. If the suicide risk is high, the crisis care manager will again arrange swift access to appropriate care. A flowchart of follow-up monitoring is provided in Fig. 3.

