### Public health impact evaluation

The public health impact of the SUPREMOCOL intervention will be evaluated, as previous studies found that it is important to not only assess the efficacy of an intervention but to also evaluate its impact [43]. For example, an intervention might be very successful in an optimal and controlled experimental condition but might have poor implementation outcomes in complex real-world settings [43]. As a result, many interventions that were found to be effective were never widely adopted in practice [44]. The evaluation to the public health impact of SUPREMOCOL will be done in terms of the five dimensions - Reach, Efficacy, Adoption, Implementation, and Maintenance - of the RE-AIM framework [43]. *Reach* refers to the extent of participation, on an individual level. It can be measured by calculating the rate of the numerator (participants) versus the denominator (population). Additionally, the representativeness of the participants can be assessed by evaluating their characteristics [43]. In this study, reach is the level in which SUPREMOCOL is used by the target population (both patients and professionals) and to their characteristics. *Efficacy* refers to the positive and negative consequences of the intervention and to behavioural and participant satisfaction outcomes [43]. In this study, changes in the outcome measures (suicidal behaviour), compliance with intervention procedures and experiences of patients and professionals with the system were measured to evaluate the efficacy of SUPREMOCOL. The proportion and representativeness of the settings that participate refer to the dimension *adoption* [43]. The level in which settings and professionals are willing to initiate the system, including their characteristics, are examined to measure this dimension in this study. *Implementation* is an individual- and intervention-level dimension and refers to the extent to which an intervention is delivered as intended [43]. In this study, implementation is defined as the level in which the system is implemented according to the protocol. The last dimension is *Maintenance*, which refers to the extent to which the intervention is part of a long-term behavioural change in individuals and organisations and has reached a stable and enduring phase [43]. Maintenance is in this study examined by an evaluation of the long-term compliance with intervention procedures and by attrition analyses.

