### Public health impact

The impact of the intervention will be evaluated in terms of the five dimensions - Reach, Efficacy, Adoption, Implementation, and Maintenance - of the RE-AIM framework [43]. All dimensions will be evaluated for each of the four pillars of SUPREMOCOL, which are 1) developing and implementing a monitoring system with decision aid to support professionals in reporting, assessing and monitoring people at risk for suicide, 2) providing swift access to people registered in the monitoring system by specialist crisis teams of SMHIs, 3) positioning of nurse care managers to collaborate with psychiatrists in assessment, case management, and guidance to treatment according to the collaborative care model, and 4) providing telephone monitoring at five fixed times during 1 year to people registered in the monitoring system to enhance adherence to treatment. The RE-AIM dimensions and the variables for the SUPREMOCOL study are presented in Table 2.

**Table 2 Tab2:** Dimensions and definitions of the RE-AIM framework with variables and data sources

Dimension & definition	SUPREMOCOL pillar	Variable	Data source
Reach			
“Proportion of the target population that participated in the intervention” [43]	Pillar 1: monitoring system	• The number (+ characteristics) of chain partners that collaborate in the system versus the number of chain partners that have been approached for collaboration	• Monitoring system • Project group logs
		• The number (+ characteristics) of SMHI’s that collaborate in the system versus the number of SMHI’s that have been approached for collaboration	• Monitoring system • Project group logs
	Pillar 2: swift access	• The number of SMHI’s which are considering swift access versus the total number of participating SMHI’s	• Project group logs • SMHI
	Pillar 3: collaborative care	• The number of SMHI’s which are considering to work according to the collaborative care model versus the total number of participating SMHI’s	• Project group logs • SMHI
	Pillar 4: 12 months follow up	• The number of SMHI’s which are considering to provide 12 months follow up versus the total number of participating SMHI’s	• Monitoring system • SMHI
Efficacy			

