“Success rate if implemented as in guidelines; defined as positive outcomes minus negative outcomes” [43]	Pillar 1: monitoring system Pillar 2: swift access Pillar 3: collaborative care Pillar 4: 12 months follow up	• Changes (both positive and negative) in primary and secondary outcome measures (suicidal behaviour), as described in the Methods section	• National and regional health records • PHQ-9 • SIDAS • Monitoring system
		• Experiences of patients and professionals regarding facilitating or hindering factors, as described in the Methods section	• Online surveys • Regular meetings
Adoption			
“Proportion of settings and practices that will adopt this intervention” [43]	Pillar 1: monitoring system	• The number (+ characteristics) of chain partners that made use of the monitoring system versus the number of chain partners who have received an account to this system	• Monitoring system
		• The number (+ characteristics) of SMHI professionals that made use of the monitoring system versus the number of SMHI professionals who have received an account to this system	• Monitoring system
	Pillar 2: swift access	• The number of SMHI departments that have the intention to provide swift access versus the total number of participating SMHI departments	• SMHI
	Pillar 3: collaborative care	• The number of SMHI nurses that have the intention to work according to the collaborative care model versus the total number of SMHI nurses in the SMHI treatment departments	• SMHI
	Pillar 4: 12 months follow up	• The number of SMHI professionals that have the intention to provide follow up contacts versus the total number of SMHI professionals who received an account to the monitoring system	• SMHI
Implementation & Maintenance			
Implementation “Extent to which the intervention is implemented as intended in the real world” [43] Maintenance “Extent to which a program is sustained over time” [43] *Implementation and Maintenance comprise the same variables, however, Maintenance will be measured at nine months.*	Pillar 1: monitoring system	• The number of successful registrations in the monitoring system versus the total number of people attempting suicide (and were in need of an ambulance ride)	• Monitoring system • Ambulance records
		• The number of first contacts that actually took place versus the number of eligible persons for a first contact	• Monitoring system

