		• The number of days, after the day on which the first contact should have taken place, the SMHI professional tried to contact the registered person	• Monitoring system
		• The number of days, after the day on which the first contact should have taken place, the first contact between the registered person and the SMHI professional actually took place	• Monitoring system
	Pillar 2: swift access	• The number of crisis assessments or psychiatric consults that were provided by the SMHI professionals versus the total number of crisis assessments or psychiatric consults that were indicated	• Monitoring system
		• The number of swift accesses to care that were arranged by the SMHI professionals versus the total number of swift accessses that were indicated	• Monitoring system
		• The number of clinical admissions that were arranged by the SMHI professionals versus the total number of admissions that were indicated	• Monitoring system
		• The number of people that was referred to their general practitioner by the SMHI professionals versus the total number of people that needed to be referred to their general practitioner	• Monitoring system
	Pillar 3: collaborative care	• The number of SMHI professionals that are involved as case managers versus the total SMHI professionals that have an account to the monitoring system	• Project group logs
		• The number of contacts with the general practitioner by the SMHI professionals versus the total of contacts with the general practitioner that were indicated	• Monitoring system
		• The number of contacts with the psychiatrist by the SMHI professionals versus the total of contacts with the psychiatrist that were indicated	• Monitoring system
	Pillar 4: 12 months follow up	• The number of eligible persons for a follow-up monitoring contact versus the number of follow-up monitoring contacts that actually took place	• Monitoring system
		• The number of days, after the day on which the follow-up monitoring contact should have taken place, the SMHI professional tried to contact the registered person	• Monitoring system
		• The number of days, after the day on which the follow-up monitoring contact should have taken place, the follow-up monitoring contact between the registered person and the SMHI professional actually took place	• Monitoring system

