The evaluation of Reach, Efficacy, Adoption, and Implementation will take place during implementation, in the SMHI areas that are allocated to SUPREMOCOL. Evaluation of these domains will be specified per SMHI area and per SWT period (which all last three months). The evaluation of Maintenance will take place nine months after the implementation period, will also last three months and will be evaluated for all SMHI areas separate, as is presented in Table 3. Each dimension is represented on a 0% (no impact) to 100% (most optimal impact) scale. The final Impact score is the function of these five dimensions, calculated for each SMHI region and SWT period [43].

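### Three RE-AIM definitions conflict with the article's own scale and definitions: the pillar 4 follow-up item is reversed, Impact needs a Maintenance value that no period has, and Reach counts no persons

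*Protocol article*

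**What the plan says.** All places are in the protocol article.

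- **Follow-up item** (Table 2, Implementation & Maintenance, pillar 4): "The number of eligible persons for a follow-up monitoring contact versus the number of follow-up monitoring contacts that actually took place".
- **First-contact item** (same block, pillar 1): "The number of first contacts that actually took place versus the number of eligible persons for a first contact".
- **Planned contacts** (Step 3: follow-up monitoring; the last four times are in months): "The monitoring contacts take place at five fixed times, i.e. 6 weeks after registration in the monitoring system, and after 3, 6, 9 and 12".
- **Scale** (Public health impact): every dimension runs from 0%, no impact, to 100%, the best impact.
- **Impact score** (same section): "The final Impact score is the function of these five dimensions, calculated for each SMHI region and SWT period". Statistical methods repeats this per region and time period.
- **Timing** (same section): Reach, Efficacy, Adoption and Implementation are evaluated per area and per three-month period. For the fifth dimension, "The evaluation of Maintenance will take place nine months after the implementation period", in one three-month window for each area.
- **Reach, definition** (Public health impact evaluation): Reach "refers to the extent of participation, on an individual level", and "It can be measured by calculating the rate of the numerator (participants) versus the denominator (population"). In this study it covers patients and professionals. Table 2 also defines it as a share of the target population, and Intervention integrity evaluation lists that share as one of its three aims.
- **Reach, variables** (Table 2): for pillar 2, the number of institutions "which are considering swift access versus the total number of participating" institutions. Pillars 3 and 4 have the same form.
- **Use**: Intervention integrity derives the integrity score from Reach, Adoption and Implementation, with weights for the four pillars. Statistical methods puts integrity per subregion into the third stepped wedge model.

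**The concern.** A score on which 100% is best needs items that rise as delivery improves, components that exist for the unit being scored, and variables that measure what the dimension is said to measure. Each requirement fails once.

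The follow-up item runs the wrong way. The Impact score is asked for in units for which one of its five components has no value of its own. Reach can read 100% without a single person being registered, although it is meant to show how much of the target population took part.

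More than descriptive reporting is at stake. Integrity enters a model of suicides and suicide attempts. If the pillar 4 item is used as printed, an area with poor telephone follow-up is credited with higher integrity on that item, and the institution-level Reach items tell the model nothing about how many people the intervention reached.

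**Working it through.** The article gives no worked RE-AIM or integrity score, so there is no figure to reproduce. The check is arithmetic on the printed ratio with assumed counts, plus a comparison of the sections.

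**1. Follow-up item, one contact due per person.** Assume E = 100 eligible persons and C contacts made. The printed order is E/C; the first-contact order is C/E.

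| C | First-contact order, C/E | As printed, E/C |
|---|---|---|
| 100 | 100% | 100/100 = 100% |
| 80 | 80% | 100/80 = 125% |
| 50 | 50% | 100/50 = 200% |
| 25 | 25% | 100/25 = 400% |

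The printed value rises as delivery falls, and leaves the 0–100% scale once any contact is missed.

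**2. Follow-up item, contacts summed over the five planned times.** Contacts due = 5 × 100 = 500.

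| Delivery | C | As printed, E/C | Order swapped only, C/E | Contacts made / contacts due |
|---|---|---|---|---|
| 100% | 500 | 100/500 = 20% | 500% | 500/500 = 100% |
| 80% | 400 | 100/400 = 25% | 400% | 400/500 = 80% |
| 50% | 250 | 100/250 = 40% | 250% | 250/500 = 50% |

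The value now stays below 100% at these delivery levels, but it is still inverted: full delivery scores lowest. Swapping the order is not enough, because persons are set against contacts. Only a denominator of contacts due stays on the scale under both readings.

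**3. Impact score.** Components measured per area and period: Reach, Efficacy, Adoption, Implementation, so 4 of 5. Maintenance: one window per area, nine months after implementation. With five areas crossing over one at a time in periods 1 to 5, there are 1 + 2 + 3 + 4 + 5 = 15 area-periods under the intervention and 5 Maintenance values, one per area. No rule says how the one regional value is assigned to that region's periods. I could not see the content of Table 3; this step rests on the text.

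**4. Reach.** The five variables in Table 2 are:
- chain partners collaborating, against those approached;
- specialist mental health institutions (SMHIs) collaborating, against those approached;
- SMHIs considering pillar 2, pillar 3 and pillar 4 (three variables), each against participating SMHIs.

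None has persons in the numerator or the target population in the denominator. Stepped wedge trial design describes one SMHI per cluster, so per area the last three are k/1 with k = 0 or 1. Each can only be 0% or 100%.

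**5. Where each defect goes.**

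| Defect | Impact score | Integrity score and third model | Pre-post test, first two models |
|---|---|---|---|
| Follow-up item (Implementation) | yes | yes | no |
| Maintenance timing | yes | no | no |
| Reach variables | yes | yes | no |

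**The case against.** **The reversed item may be only a word-order slip.** Table 2 gives no formulas, the numerator-versus-denominator sentence is about Reach, and the other Implementation count comparisons put the achieved count first. An analyst who respects the 0–100% scale would probably turn the item round. This stands as a limit: the score is wrong only if the item is used as printed. But simply turning it round leaves the mismatch of persons and contacts.

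**The size depends on the reading.** A reader might infer that the item always exceeds 100%. That holds only with one contact due per person. Summed over five contacts, the values are 20% to 40% for full to half delivery. Only the inversion is common to both. The article has no capping rule, so nothing can be said about capped scores.

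**The delay items.** Days of delay also rise as delivery worsens, and a reader might count them as a further error. The article does not say that raw days enter a score, and their mapping to a percentage may sit in the full plan. I do not count them.

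**The Impact score is not impossible.** A region's single Maintenance value could be carried to all its periods. That is a fair answer to the claim that the score cannot be computed. The article does not state the rule, however, and such a component would not vary by period.

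**Person-level information does exist.** A reader might infer that the participation aim under integrity cannot be addressed at all. That is too strong. Under Implementation, Table 2 counts first contacts among eligible persons, referrals to the general practitioner among those needing one, and registrations against people with an ambulance-attended attempt, and Implementation feeds integrity. Still, the first two cover only people already in the system. The third can exceed 100%, because people with ideation only can also be registered. None is the share of the target population.

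**The consequence is limited.** This stands. The follow-up item is one of many within weighted pillars, and its effect on the integrity score or the third model cannot be quantified from the article.

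**Conclusion.** The point holds as three conflicts between the RE-AIM definitions and the article's own scale, timing and definitions.

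- **Follow-up item:** inverted on both readings (200% at half delivery with one contact due; 20% at full and 40% at half delivery over five contacts), and it mixes units. This assumes that versus means numerator over denominator, as the Reach text and the parallel items suggest, and uses an illustrative 100 eligible persons.
- **Impact score:** 4 of 5 components have a value for the period, and there is no rule for the fifth.
- **Reach:** none of the five variables counts persons, and three can only be 0% or 100% per area.

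The first and third reach the integrity score and the third stepped wedge model; the second affects the Impact score alone. A reader might infer that the trial's main result is at risk. The article does not support that: the pre-post comparison of completed suicides and the first two multilevel models use none of these scores. This is worth correcting because the definitions are wrong as written and cheap to repair.

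**What to change.** 1. **Pillar 4 item.** Define it as follow-up contacts made divided by follow-up contacts due, in that region and period.
2. **Impact score.** Compute a four-dimension score (Reach, Efficacy, Adoption, Implementation) per region and period. Report Maintenance, or a five-dimension score, once per region. Change the sentences in Public health impact and Statistical methods to match.
3. **Reach.** Add a person-level variable per region and period, such as persons registered relative to a stated estimate of the target population. Report registrations against ambulance-attended attempts beside it as a proxy ratio, with a note that it can exceed 100% because people with ideation only are also registered. Move the organisation counts to Adoption.

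A Reach limited to people registered after an ambulance-attended attempt would not serve as the main measure. It would leave out people with ideation only, who belong to the target population. It would also need registrations linked to ambulance records, which the article does not describe; the ambulance data appear there as a number of rides.

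The cost is small: edits to Table 2 and two sentences, and acceptance that the Reach denominator is an estimate. No new contact with participants is needed for the follow-up item, since Table 2 already names the monitoring system as its source.

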#### Statistical methods

To examine whether SUPREMOCOL leads to a reduction of completed suicides of 20% in the province of Noord-Brabant, the total number of completed suicides in the post-measurement will be compared to the total number of completed suicides in the pre-measurement. As the total number of residents in this province might have changed, we will also compare the pre- and post-incidence rates of suicides. An exact rate ratio test will be used. To take general trends over time into account, we will compare the incidence ratio in Noord-Brabant with the incidence ratios in other provinces in Noord-Brabant, and with the other provinces combined.

To examine whether SUPREMOCOL leads to a reduction of completed suicides and suicide attempts in association with the stepwise implementation of the system intervention in the subregions of the province, the total number of completed suicides and suicide attempts in each month will be compared to the two levels of our stepped wedge trial: region and time. A poison multilevel model will be used. The occurrence of completed suicide or admissions due to suicide risk in an SMHI will also be taken into account in the analysis. The suicide rates will be corrected for seasonal fluctuations [45]. In a second model, organisational differences between the regions, such as available number of crisis departments, will be taken into account. In a third model, the level of treatment integrity per subregion will be taken into account as well.

To explore whether SUPREMOCOL leads to a reduction of suicidal ideation in people registered in the monitoring system, the scores on the PHQ-9, SIDAS, and decision aid -that will be filled out by participants during the year that they receive the Supremocol additional care- will be compared by repeated measures. This will be used as exploratory process evaluation, as there is no control group for this.

To examine the impact of SUPREMOCOL with regards to reach, efficacy, adoption, implementation, and maintenance, an impact score will be calculated for each SMHI region and time period. This scores will be based on the function of all five RE-AIM dimensions, which are represented on a 0% (no impact) to 100% (best possible impact) scale [43].

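### Efficacy is defined as a net quantity that can fall below zero but is scored from 0% to 100%, so the Efficacy and Impact scores cannot show net harm

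*Protocol article*

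**What the plan says.** All statements are in the protocol article.

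- **What Efficacy is.** Table 2, under Public health impact, describes it as a success rate "defined as positive outcomes minus negative outcomes". The first variable listed is "Changes (both positive and negative) in primary and secondary outcome measures (suicidal behaviour), as described in the Methods section". Experiences of patients and professionals are a second variable. The section Public health impact evaluation agrees: Efficacy "refers to the positive and negative consequences of the intervention and to behavioural and participant satisfaction outcomes".
- **How it is scored.** Public health impact states: "Each dimension is represented on a 0% (no impact) to 100% (most optimal impact) scale". Statistical methods repeats the same limits for all five dimensions.
- **The unit.** Reach, Efficacy, Adoption and Implementation are evaluated for each area in each stepped wedge period, and each period lasts three months.
- **How it is used.** The five dimensions are combined, and "an impact score will be calculated for each SMHI region and time period". The combining function is not written out; a cited source is given for it.

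The article gives no rule for an Efficacy result below zero.

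**The concern.** Reach, Adoption and most of the Implementation variables are proportions, and a 0-100% scale suits them. Efficacy is a difference between gains and losses. Its natural zero lies inside its range, whereas the scale puts zero at the bottom and labels it as no impact. A period with more suicides or attempts than expected cannot be told apart from one with no change.

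The unit of scoring adds a second problem. One area in one quarter yields few suicides, so observed changes swing widely by chance. If falls are credited and rises are recorded as zero, the average score is above zero even when nothing has changed.

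At stake is the public health impact evaluation, one of the three elements named under Study design. The Discussion says its information is meant to help judge the efficacy of the intervention.

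**Working it through.** **Step 1. The texts side by side.** The definition is signed, and the variable covers changes in both directions. The scale has no value below 0%, and 0% means no impact. Both cannot hold when losses exceed gains. Moving the neutral point to 50% would not reconcile them, because it contradicts the label on 0% and gives an ineffective intervention a score of 50%.

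**Step 2. Direction of the chance effect.** A score that can never be negative and is sometimes positive has a mean above zero when the true effect is nil. This holds for any mapping with a floor at zero.

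**Step 3. Size, as an illustration.** The article states no figure for the Efficacy score, so there is none to reproduce.

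Inputs from the article:
- 365 suicides in the province in 2017 (Sample size)
- five clusters (Stepped wedge trial design)
- three-month periods (Public health impact)
- a 20% target reduction (Hypotheses)

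Assumptions, not in the article:
- the five areas are equal in size
- suicides are the only input to Efficacy
- negative values are set to zero
- the baseline is one quarter or one year in the same area
- counts are Poisson

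Expected suicides per area and quarter: 365 / 5 / 4 = 18.25.

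Score = max(0, 1 - X/B), where X is Poisson with mean 18.25 × RR. B is a Poisson count with mean 18.25 (one quarter), or one quarter of a Poisson count with mean 73 (one year). Exact enumeration gives:

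| True effect | Mean floored score, one-quarter / one-year baseline | Cells scoring above 0 |
|---|---|---|
| None (RR 1.0) | 11.1% / 9.9% | 47% / 50% |
| 20% reduction (RR 0.8) | 22.1% / 22.1% | 71% / 79% |
| 20% increase (RR 1.2) | 4.8% / 3.5% | 26% / 24% |

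With no effect, a reduction of 20% or more appears by chance in 26% / 22% of cells.

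Hand check for no effect: the relative change has an approximate SD of √(2/18.25) = 0.33 with a one-quarter baseline, or √(1.25/18.25) = 0.26 with a one-year baseline. The positive part of a centred normal variable has mean 0.40 × SD, so about 13% / 10%. This is close to the exact values.

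**Step 4. What the floor removes.** If negative values are kept, the mean with no effect is -6% / -1%. The small negative values come from dividing by a random count. With a true 20% increase the mean is -27% / -22%, so the harm is visible.

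**Step 5. Sensitivity, no effect.**
- Unequal areas, with 8 to 30 expected suicides per cell: mean floored score 8% to 16%.
- 293 suicides a year, the 2014 figure in the Background (14.65 per cell): 12.2% / 11.0%.
- A commoner outcome such as attempts, at an illustrative 100 per cell (the article gives no attempt counts): 5.2% / 4.3%.

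**The case against.** The strongest reply is that the scored quantity above is a construction. The article does not say that Efficacy equals a truncated relative change in suicides. It lists several inputs, including attempts, questionnaire scores and user experience, sets no reference period for Efficacy, and refers the scoring to a cited source. A journal article may leave such detail to a fuller document. This stands as far as size is concerned. The percentages are illustrative, they shrink with commoner outcomes, and the experience items are not modelled. It does not remove the conflict, because the definition, the limits of the scale and the label on its lowest point are all printed in the article.

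A reader might infer that the trial as a whole is blind to harm. The documents do not support that. The exact rate ratio test, the comparison with other provinces and the multilevel Poisson model have no floor, and Harms requires each suicide in a registered person to be reported and assessed. A reader might also fear that the fault reaches the third Poisson model through the integrity score, but that score is derived from Reach, Adoption and Implementation only.

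It is also fair to say that the public health impact work is described under Objectives as exploratory, and that no hypothesis or decision rule uses the Efficacy or Impact score.

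**Conclusion.** The point holds in a limited form. The definition of Efficacy and its scale contradict each other, and as written neither the Efficacy score nor the Impact score can show net harm. This part needs no assumption about the data.

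The upward bias is conditional on negative values being set to zero. Under the assumptions listed, an ineffective intervention averages about half the score of one that meets the 20% target. This is a statement about averages: about half of the cells score zero when there is no effect, so it does not follow that every area shows efficacy. The bias in the Impact score cannot be sized, because its function is not given.

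The consequence is confined to these two exploratory scores. It is worth correcting because a summary of a suicide prevention programme should be able to register more suicides.

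**What to change.** In Public health impact and in Statistical methods, exempt Efficacy from the 0-100% floor. Report it as a signed effect: the rate ratio with its confidence interval from the analyses already planned, presented so that an increase in suicides or attempts shows as negative. A log rate ratio would also avoid most of the small downward bias of a simple ratio seen in Step 4.

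Then choose one of two ways to handle the Impact score and state it:

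1. let the Impact score take a negative Efficacy value; or
2. show Efficacy beside an area-by-period score built from the other dimensions. The integrity score already combines Reach, Adoption and Implementation.

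The cost is a change of wording in two places and no new data. The downside is small: the single 0-100% five-dimension score for each area and period is changed or dropped.
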